# Herbst appliance with skeletal anchorage versus dental anchorage in adolescents with Class II malocclusion: study protocol for a randomised controlled trial

**DOI:** 10.1186/s13063-017-2297-5

**Published:** 2017-11-25

**Keywords:** Activator appliances, Dental implants, Orthodontic appliances, Orthodontic anchorage Procedures

## Abstract

**Background:**

The Herbst appliance is an orthodontic appliance that is used for the correction of class II malocclusion with skeletal discrepancies. Research has shown that this is effective. However, a potential harm is excessive protrusion of the lower front teeth. This is associated with gingival recession, loss of tooth support, and root resorption. This trial evaluates a method of reducing this problem.

**Methods/Design:**

The study is a single-center, randomised, assessor-blinded, superiority clinical trial with parallel 1:1 allocation. Male and female young people (10–14 years old) with prominent front teeth (class II, division 1) will be treated in one orthodontic clinic. Group 1 will be treated with the conventional Herbst appliance with dental anchorage and group 2 with the Herbst appliance with indirect skeletal anchorage for 12 months. The primary objective will be to compare the proclination of the lower incisors between the Herbst appliance with dental anchorage and skeletal anchorage. Secondary objectives will be to evaluate the changes occurring between the groups in the mandible, maxilla, lower and upper molars, and in gingival recession and root resorption at the end of the treatment. Additionally, the young patient’s experience using the appliances will be assessed. The primary outcome measure will be the amount of lower incisor proclination at the end of treatment. This will be assessed by cone-beam computed tomography (CBCT) superimposition. Secondary outcome measures will be the changes in the mandible, maxilla, lower and upper molars at the end of treatment assessed by tomography superimposition and the young patient’s experience using the appliances assessed by self-reported questionnaires and semi-structured interviews. The randomisation method will be blocked randomisation, using software to generate a randomised list. The allocation concealment will be done in opaque envelopes numbered from 1 to 40 containing the treatment modality. The randomisation will be implemented by the secretary of the Department of Orthodontics of Rio de Janeiro State University before the beginning of the study. The patients and the orthodontists who will treat the patients cannot be blinded, as they will know the type of appliance used. The technician who will take the CBCT image and the data analyst will be blinded to patients’ group allocation.

**Discussion:**

If this new intervention is effective, the findings can change orthodontic practice and may also be relevant to other forms of treatment in which appliances are fixed to the bones of the jaws. However, if the bone anchoring is not effective, the trial will provide much needed information on the use of this comparatively new development.

**Trial registration:**

ClinicalTrials.gov, protocol ID: NCT0241812. Registered on 26 March 2015.

**Electronic supplementary material:**

The online version of this article (doi:10.1186/s13063-017-2297-5) contains supplementary material, which is available to authorized users.

## Background

Orthodontic treatment is directed at the treatment of malocclusion. This may range from the correction of a few crooked teeth to severe problems associated with craniofacial anomalies. One of the most common orthodontic problems is prominent upper front teeth (class II malocclusion). The prevalence of this condition is high and comprises approximately 50% of orthodontic problems [1, 2]. Prominent teeth are associated with low perception of appearance. This may result in psychosocial problems and teasing [3]. Furthermore, upper front teeth are at risk of being traumatised with subsequent damage or even loss.

Different types of braces have been developed for the treatment of class II malocclusion. These are called functional appliances and they correct the position of the incisor teeth. A popular type of functional appliance is the Herbst appliance. This is fixed to the teeth and has been shown to be very effective. Nevertheless, there are concerns that this appliance can result in harm to the teeth and supporting bone. This is because it moves the lower incisors forwards (proclination). This may result in recession of the gums, resorption of the roots and general concerns about the long-term health of the lower incisors [4–10].

With the intention of solving these problems, we developed a version of the Herbst appliance that is fixed to the bone of the lower jaw and not attached to the teeth (skeletal anchorage); thus, removing the forward directed force on the lower incisors [11–14].

## Methods

### Objectives

#### Primary objective

The primary objective is to compare the effects of the Herbst appliance with either skeletal anchorage or dental anchorage on the position of the lower incisors in the treatment of young people with class II malocclusion.

#### Secondary objectives

To evaluate the changes that occurred in the mandible and maxilla, the relationship between the maxilla and mandible, lower molars and upper molars, and in gingival recession and root resorption at the end of the treatment with the Herbst appliance with skeletal and dental anchorage in patients with class II malocclusionTo explore young people’s experience of using the two types of Herbst appliance

### Design

The study is a single-center, randomised, assessor-blinded, superiority clinical trial with parallel 1:1 allocation. It involves children with class II malocclusion. We will randomise 40 children aged from 11 to 14 years old to treatment with a Herbst appliance with either dental or indirect skeletal anchorage. All participants will be followed until the end of the functional (Herbst) appliance phase of treatment. The expected flow of patients through the trial can be seen in Fig. 1. The SPIRIT checklist with the recommended items to address in a clinical trial protocol is available (Additional file 1).

**Fig. 1 Fig1:**
[figure not shown]
Flow chart with projected numbers of participants throughout the trial. Group 1: Herbst appliance with dental anchorage and group 2: Herbst appliance with skeletal anchorage. *ITT* intention-to-treat

### Setting

#### Participants

Young people aged from 10 to 14 years old with class II malocclusion are eligible to join the trial if they meet the following inclusion criteria:

#### Inclusion criteria

The eligibility criteria for inclusion in the trial will be:Aged from 10 to 14 years old and attending the Universidade do Estado do Rio de Janeiro (UERJ) Orthodontics Clinic at the peak of the pubertal spurt assessed using vertebral analysisFeatures of a class II, division 1 malocclusion with a convex profile and minimum overjet of 6 mm in permanent dentition, without missing teethParental informed consent

For the administering of self-reported questionnaires and semi-structured interviews, the participants will be recruited after they have completed the treatment. The intention will be to speak to all the young people who took part in the trial in the hope of achieving the theoretical data saturation point. A researcher with experience in conducting qualitative research will get in touch with young people via telephone. The researcher will explain the purpose of the interviews to the young people and invite them to take part in the study. The young people will be given at least 48 h to consider their decision and the researcher will call back to confirm the decision.

#### Exclusion criteria

Young people with any of the following are not eligible for inclusion in the trial:Previous orthodontic or orthopaedic treatment with any type of intervention (to avoid confounding factors related to previous treatment)Syndromes, orofacial cleft, or other special needsMissing teeth (to avoid confounding factors related to anchorage loss due to the absence or early extraction of permanent teeth)Poor oral health that precludes orthodontic treatment (presence of caries, active white spots or periodontal diseases)

### Recruitment

The recruitment period will be between August 2015 and August 2018. The strategies for achieving adequate participant enrolment to reach target sample will be:Search the waiting file of the UERJ Orthodontics ClinicReferral from other public institutionsPrivate clinics and public schools

#### Registration and consent

The clinical orthodontist will screen eligible children. If a young person is eligible, the clinician will outline a verbal description of the trial to the young person and their parent/legal guardian. If they are interested in taking part in the trial, the clinician will ask them to give written informed consent. The young people will then give time to read the written informed consent information and ask any questions. The parents/legal guardians who consent to take part will complete the Consent Form, which will also be signed by the young person and the clinician. The parents/legal guardians will be informed that they have the right to withdraw from the trial at any time with the guarantee that their clinical care will not be compromised neither additional costs will be done.

A copy of the written Consent Form will be given to the representatives, and another one will be kept with the investigators who will keep an anonymous screening log of all ineligible and eligible participants who did not consent to take part in the study.

### Locations

The trial will be carried out in the UERJ Orthodontic Clinic, Rio de Janeiro, Brazil. This public university serves a predominantly low-income population located in the Vila Isabel neighbourhood in northern Rio de Janeiro State, Brazil. The estimated population size is 81,858 habitants (IBGE – CENSO 2000). Data will be collected from August 2015 through August 2018.

### Trial intervention

Two groups will receive treatment. Group 1 will be treated with the Herbst appliance with dental anchorage for 12 months (Fig. 2). Group 2 will be treated with the Herbst appliance with skeletal anchorage in mini-implants for 12 months (Fig. 3). Only the Herbst phase will be studied to reflect just the changes caused for the orthopaedic appliance.

**Fig. 2 Fig2:**
[figure not shown]
Herbst appliance with dental anchorage

**Fig. 3 Fig3:**
[figure not shown]
Herbst appliance with skeletal anchorage

#### Group 1

The Herbst appliance in group 1 will be the ‘cast splint’ type, made in cobalt-chromium (Herbst I set, Dentaurum, Ispringen, Germany). Group 1 will be anchored from the second molars to the first premolars in the upper arch and from the second molars to cuspids in the lower arch, following the Giessen University protocol [10].

At the first appointment, impressions from the upper and lower teeth will be taken with alginate (Orthoprint, Zhermack, Badia Polesine, Italy). Next, a construction-bite will be taken with wax. Then, the impressions and the registration will be sent to the laboratory for the construction of the Herbst appliance. The Herbst appliance will be placed on the second appointment.

#### Group 2

The Herbst appliance in group 2 will be the same as in group 1. However, its lower part will be anchored to mini-implants using 0.012" stainless-steel ligature wire (Morelli, Sorocaba, São Paulo, Brazil) from the mini-implants to a bracket soldered to the Herbst appliance on the buccal side of the cuspids.

Before placing the mini-implants, a cone-beam computed tomogram (CBCT) will be taken using Classic iCAT tomography (Image Sciences, Hatfield, PA, USA), to select the best site for insertion. We will then insert two self-tapping mini-implants (Neodent, Curitiba, Brazil), 2 mm in diameter × 10 mm in length, with attachments for the Herbst appliance telescopic tubes, between the roots of the cuspids and the first premolars or between the roots of the first and second premolars on each side, on the alveolar ridge through attached gingiva.

A lower rotation handpiece with torque control and a cone-shaped burr 1.3 mm in diameter (Neodent, Curitiba, Brazil) will be used to make a guide from the buccal to the lingual cortical bone in order to achieve bicortical anchorage. After the insertion of the mini-implants, new radiographs will be taken using the parallel technique to check if the mini-implants were inserted in the correct position.

### Analysis

#### Sample size

The primary outcome measure is the difference between the post- and pre-treatment position of the lower incisor edge calculated in millimeters. A 2-mm difference in primary outcome between groups is considered to be clinically significant. This value was obtained based on the clinical judgment of 18 dental professors, senior and junior lecturers, and post-graduate students via interviewing. The standard deviation of such difference was reported in the academic literature to be 1.65 [15]. Allowing for 5% type 1 error, 90% power and equal size allocation among groups, 32 subjects will be required. Considering a 20% attrition rate the total number of recruitment will be 40, with 20 in each group. This calculation was done using online open source software developed by Harvard University [16].

### Randomisation

#### Sequence generation

The randomisation schedule will be prepared and comprise random blocks that are stratified by gender. As a result, the sample will be separated into 10 blocks with four subjects in each.

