#### Allocation and concealment mechanism

Allocation sequence will be concealed in sequential opaque envelopes numbered from 1 to 40, with the treatment allocation.

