### Implementation

Patients who fulfil the inclusion criteria will be consented before the randomisation. The secretary in the Department of Orthodontics of the Faculty of Dentistry from Rio de Janeiro State University will be responsible for the implementation of the randomisation (generation and storage of the randomised list, allocation, concealment, and treatment assignment). The subjects will write their names on the numbered envelopes and will open them to know the treatment for which they were selected. After that, the envelopes will be closed with the type of treatment selected for storage of the information.

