### Blinding

Due to the nature of the treatment, the patients cannot be blinded to the allocation group. Similarly, the orthodontists who will treat the patients cannot be blinded, as they will know the type of appliance used. However, the technician who will take and analyse the CBCT image will be blinded to the allocation cone because the images will not include the appliance. The data analyst will be blinded to group allocation.

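### As described, the randomisation does not deliver the stated gender stratification, and its single fixed block size of four makes some allocations deducible

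*Protocol article*

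**What the plan says.** Under Sequence generation, the protocol article states that the schedule will "comprise random blocks that are stratified by gender". The next sentence presents the block structure as the consequence: "As a result, the sample will be separated into 10 blocks with four subjects in each".

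Under Allocation and concealment mechanism, there is one numbering: "Allocation sequence will be concealed in sequential opaque envelopes numbered from 1 to 40, with the treatment allocation". The Abstract (Methods/Design) gives the same range of envelope numbers and calls the method blocked randomisation, without mentioning stratification.

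The surrounding arrangements bear on concealment:

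- **Recruitment.** Under Registration and consent, "The clinical orthodontist will screen eligible children", and the clinician obtains consent.
- **Custody.** Under Implementation, consent precedes randomisation, and a department secretary generates and stores the list and assigns treatment.
- **Opening.** Also under Implementation, "The subjects will write their names on the numbered envelopes and will open them to know the treatment for which they were selected".
- **Blinding.** Under Blinding, "the orthodontists who will treat the patients cannot be blinded, as they will know the type of appliance used".

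The Design section describes a single-centre trial with 1:1 allocation.

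**The concern.** Stratified blocking needs a separate sequence of blocks within each stratum. Each sequence must be long enough for however many boys or girls arrive. Ten blocks of four for 40 patients in one numbered series is what blocking without stratification looks like. The two descriptions fit together only under a rule that the article does not give.

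Two things are at stake. The first is the balance on gender that the investigators chose to build in, in a trial with only 20 per arm. The second is concealment. With one known block size, each completed block reveals where the next one starts, and the last one or two assignments of a block can be deduced from those before. In one clinic with unblinded orthodontists, that leaves an opening for selection bias.

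**Working it through.** **The plan's own figures.** 32 / (1 − 0.20) = 40, and 10 × 4 = 40. Both reproduce, and the sample size is not in question here.

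**Inputs.** From the article: 40 patients, 1:1, ten blocks of four, envelopes 1 to 40. Assumed: the proportion of girls, taken as 30 to 60% because the article gives no split.

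**Reading A: one series opened in order of arrival.** Ten complete blocks give exactly 20 per arm. Gender plays no part in the allocation, so the number of boys in each arm is an independent Binomial(20, p). A surplus of boys in one arm is an equal surplus of girls in the other, so the absolute difference is the same for both genders.

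| Proportion of one gender | P(difference ≥ 4) | P(difference ≥ 6) |
|---|---|---|
| 30% | 22.6% | 5.6% |
| 40% or 60% | 25.8% | 7.5% |
| 50% | 26.8% | 8.1% |

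A simulation of 20,000 trials per setting agrees: 23 to 26% for a difference of 4 or more. With separate blocks of four for each gender, only the last, incomplete block in a stratum can be unbalanced, so the difference never exceeds 2. Its simulated mean is about 0.7, against 2.3 to 2.5 for the single series.

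**Reading B: envelopes reserved by gender, five blocks each.** This does stratify. It fills exactly 40 only if recruitment gives 20 boys and 20 girls:

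- at 50% girls, C(40,20) × 0.5^40 = 12.5%
- at 40% or 60% girls, C(40,20) × 0.4^20 × 0.6^20 = 5.5%

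If whole blocks could go to either gender as needed, exactly ten complete blocks would still require the number of boys to be a multiple of four. That has a probability of about 25%.

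**Predictability of a fixed block of four, past allocations known.**

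- *Certain assignments.* The fourth is always determined. The third is determined when the first two match, with probability 1/3. The share is (1 + 1/3)/4 = 33.3%, or about 13 of 40.
- *Best guess (the arm that is behind).* (1/2 + 2/3 + 2/3 + 1)/4 = 70.8% correct, against 50% without blocking.

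Separate series for boys and girls would leave these shares unchanged within completed blocks.

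**Effect of varying the block size.** With sizes 2, 4 and 6 equally likely, expected correct guesses per block are 1.5, 2.83 and 4.1, so the rate is 8.43/12 = 70.3%. Best-guess success hardly moves. The gain is in certainty: an observer who does not know where a block ends can seldom be sure of the next assignment.

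**The case against.** A reader might infer that the scheme cannot stratify at all. The documents do not support that. Ten blocks of four under one numbering are compatible with stratification if the envelopes are divided by gender, and the article neither describes nor excludes this. A journal article may also leave the handling of envelopes to the full protocol. What remains is that the article does fix the number of blocks, their size and the envelope range, and under those figures stratification needs an unstated quota or spare envelopes.

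A reader might also infer that recruiters see every allocation and can predict the next. That is not stated either. The screening orthodontist and the treating orthodontists are not said to be the same people. The secretary holds the list, the envelopes are opaque, and consent comes before randomisation. These safeguards protect the contents of the next envelope, but they do not prevent deduction by someone who learns earlier allocations. The 33% is therefore an upper bound. Publication of the block size adds little: the article is dated 25 November 2017, so it could affect only about the last 9 of 36 months of recruitment.

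Finally, chance imbalance in gender is not bias in the outcome. Eligibility is confined to the peak of the pubertal spurt, an analysis allowing for potential confounders is planned, CBCT assessment is blinded, and nothing in the article shows that incisor displacement depends on gender. All of this stands and limits the consequence. It does not make the description consistent.

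**Conclusion.** The point holds as a defect in the randomisation as described. The stated gender stratification does not follow from ten blocks of four in one series numbered 1 to 40. Used in order, the series leaves a difference of 4 or more boys between arms in about 23 to 27% of trials, given 30 to 60% of one gender. Divided 20/20, it fills exactly in 12.5% of cases at 50% girls and 5.5% at 40% or 60%. The two sets of figures belong to alternative readings and should not be combined.

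Predictability is a separate and smaller matter: at most 33% of assignments are certain, and only to a recruiter who knows all past allocations. The documents show neither that this knowledge existed nor that selection bias occurred. The primary comparison remains a randomised one.

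**What to change.** Reconcile Sequence generation with Allocation and concealment mechanism in one of two ways:

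1. Use separate envelope series for boys and girls, each with enough envelopes for any split (40 in each would cover every case), and stop at 40 patients in total. Delete the statement of ten blocks of four.
2. Drop the stratification claim and report the trial as blocked only.

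For envelopes not yet opened, use randomly varying block sizes and withhold them from recruiting staff. State plainly that this mainly reduces certain assignments and leaves best-guess success at about 70%. Report the method actually used for the patients already allocated, and the date of any change.

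The cost is a new list and extra envelopes. Stopping at 40 can also leave incomplete blocks: with two strata and blocks of four, the arms can differ by up to 2 + 2 = 4 patients, and with blocks of up to six by 3 + 3 = 6. The change would fall mid-trial, may cut a block short, and would reach only the remaining allocations. Under even accrual, and counting from publication, that is about 40 × 9/36 = 10 patients.

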#### Allocation and concealment mechanism

Allocation sequence will be concealed in sequential opaque envelopes numbered from 1 to 40, with the treatment allocation.

### Implementation

Patients who fulfil the inclusion criteria will be consented before the randomisation. The secretary in the Department of Orthodontics of the Faculty of Dentistry from Rio de Janeiro State University will be responsible for the implementation of the randomisation (generation and storage of the randomised list, allocation, concealment, and treatment assignment). The subjects will write their names on the numbered envelopes and will open them to know the treatment for which they were selected. After that, the envelopes will be closed with the type of treatment selected for storage of the information.

